## **8-2. Primary Endpoint Analyses**

1) The main objective of this study is to evaluate the superiority of the study drug in terms of the disease-free survival (DFS) of group B (test treatment group: 16 courses administered) compared with group A (standard treatment group: 8 courses administered). The median annual DFS for all enrolled subjects is estimated by group using the Kaplan-Meier method. Greenwood’s formula is used for interval estimation. For the evaluation of the hypothesis, the stratified log-rank test, which considers a layer composed of a combination of allocation adjustment factors excluding study sites, is used. If the one-sided significance level is 5% and it is demonstrated that group B exhibits statistically significantly superior performance compared with group A, group B will be regarded as the standard therapy replacing the group A therapy. If group B’s performance is inferior to group A, the standard therapy will remain unchanged.

2) The stratified Cox proportional hazard model will be used. This model considers the layer composed of the combination of allocation adjustment factors other than study site as an estimate of the treatment effect. The hazard ratio of the treatment effect among the groups and its 95% confidence interval will also be obtained. A Wald-type estimator is used to estimate confidence intervals. If necessary, in addition to the allocation adjustment factor, an adjusted hazard ratio accounting for background bias will be derived.

3) A similar secondary analysis will be carried out for all eligible subjects.

## **8-3. Secondary Endpoint Analyses**

1) DFS, relapse-free survival (RFS), and overall survival (OS) are evaluated using the same analysis.

2) An estimate of 2-year DFS rate is derived from the DFS Kaplan-Meier curve.

3) Adverse events are tabulated for each group, and the onset frequency of adverse events in the standard treatment group and the test group will be compared. However, no hypothesis testing will be conducted.

4) Drug adherence is calculated based on the rate of individual drug adherence and actual dosage per actual administration period, and is compared between the groups.

5) Summary statistics regarding total treatment costs will be estimated and compared between the groups. However, no hypothesis testing will be conducted.

## **8-4. Target Number of Subjects and Statistical Basis**

Number of target subjects: 1,200 subjects (1 group: 600 subjects)

The main objective of this study is to evaluate the superiority of the study drug in terms of the DFS of group B (test treatment group: 16 courses administered) compared with group A (standard treatment group: 8 courses administered). There is no difference in disease-free survival (DFS) during this 6-month period since group A and group B receive essentially the same 6-month treatment after randomization, and differences in DFS between the groups are expected to appear 6 months after randomization.

When designing the number of subjects assuming a normal exponential distribution without considering the above, the number of required subjects is underpowered. Therefore, in this study, the number of subjects was established assuming a segmented exponential model. In the 6 months following randomization, the hazard ratios for DFS in group A and group B were the same, and assuming that differences in DFS begin to appear after 6 months, the 5-year DFS rate in group A will be 56–62%. In group B, if 5% or 7% is expected to be added to the 5-year DFS rate of group A, the number of required subjects is as follows, with a one-sided significance level of 5% and a detection power of 80% (Table 8-1). The power function of the Statistical Analysis System (SAS) ver.9.1 was used to determine the appropriate number of subjects for this study.

Table 8-1 With a 2-year enrollment period and 5-year follow-up period

| 5-year disease-free survival rate (Group A) | 5-year disease-free survival rate (Group B) | |
| --- | --- | --- |
| 5% increase | 7% increase |
| 56% | 2,394 patients | 1,206 patients |
| 58% | 2,336 patients | 1,176 patients |
| 60% | 2,272 patients | 1,142 patients |
| 62% | 2,202 patients | 1,104 patients |

Table 8-2 With a 3-year enrollment period and 5-year follow-up period

| 5-year disease-free survival rate (Group A) | 5-year disease-free survival rate (Group B) | |
| --- | --- | --- |
| 5% increase | 7% increase |
| 56% | 2,288 patients | 1,152 patients |
| 58% | 2,228 patients | 1,120 patients |
| 60% | 2,164 patients | 1,086 patients |
| 62% | 2,092 patients | 1,048 patients |

Since the 5-year DFS rate in the X-ACT study was 60.8%, assuming that the 5-year survival rate for group A is 60% and that the 5-year survival rate in group B is 67%, with 2 years of enrollment and 5 years of follow-up, a detection power 80%, and a one-sided significance level of 5%, 1,142 subjects (480 events) across the 2 groups are necessary. However, the number of required events was estimated based on a simulation. Also, contrary to expectations, even if the 5-year survival rate for group A is 56%, a detection power of 74% can be achieved with 480 events.

Assuming a dropout rate during the test period of approximately 5%, the number of target subjects in the 2 study groups is set to 1,200 (600 per group).

## **8-5. Revision to the Number of Subjects**

Patient prognosis in Japan may be better than that of the X-ACT study owing to differences in patient background and surgical results. Therefore, we estimated DFS Kaplan-Meier curves for both groups using the latest data as early as possible before enrolling the target number of subjects and compared the curved against those of the X-ACT. As a result of comparing the annual survival rate, patient background, etc. with the results of the X-ACT trial, the number of subjects in this study will be revised if it is determined that event occurrences are clearly inadequate.

When redesigning the number of subjects, the magnitude that appears to be clinically appropriate will be reviewed as an additional effect expected for group B against the 5-year DFS rate for group A.

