## **8-7. Interim Analyses and Early Study Termination**

Three interim analyses were conducted for the purpose of evaluating whether enrollment can be continued and whether the primary endpoint of the study has been achieved. The first interim analysis will be performed after half of the number of subjects are enrolled. This analysis will comprehensively evaluate whether enrollment should be continued. However, the effectiveness of the first intermediate analysis is not evaluated. As a general rule, registration will not be suspended during interim analysis.

In the second interim analysis, the main purpose is to evaluate study effectiveness, and this analysis is performed after the 1,200 subjects are enrolled. The second interim analysis will also involve an exploratory analysis that will serve as a reference for the secondary comparative study of the 2-year DFS rate. In this exploratory evaluation, the selection design 31) described by R. Simon is applied, and the selection results are disclosed only to the members of the Data and Safety Monitoring Committee and the researchers recognized by the Executive Committee. However, this disclosure will not affect the verifiability of the primary endpoint of this study, and these results will also be published in the interim analysis.

In the third interim analysis, the main purpose is to evaluate the effectiveness of the study, and this analysis will be conducted after half the number of necessary events (240 events) are observed during the follow-up period. If it is determined that the primary endpoint of the study has been achieved during interim analysis, the study will be terminated and the results of the study will promptly be made public at academic symposia and in academic journals.

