Interim analyses are carried out by the data center. To maintain the overall Type I error rate at 5%, test multiplicity for the interim and final analyses was adjusted using Lan & DeMets’ α consumption function 32). The difference in DFS between the groups was examined for statistical significance, but here the O’Brien & Fleming type was used as the α consumption function. During intermediate analysis, when the DFS for group B exceeded that of group A and the one-sided *p*-value of the stratified log-rank test fell below the significance level prescribed by the above method, the result was determined to be statistically significant and the test was terminated as a general rule. If the survival curve for group B is lower than that of group A, judgments are not made based on test results, and the issue of whether to comprehensively terminate the study is made with reference to estimated Bayes flow probability or conditional detection ability.

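### Section 8-5 allows the sample size and the expected Group B effect to be revised with by-arm DFS curves in view, outside the alpha-spending plan

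*Protocol*

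**What the plan says.** Section 8-4 sets the size from 5-year DFS of 60% in Group A against 67% in Group B, with one-sided 5% significance and 80% power. It assumes no difference between the arms for the first half-year: "In the 6 months following randomization, the hazard ratios for DFS in group A and group B were the same". The result is that "1,142 subjects (480 events) across the 2 groups are necessary", raised to 1,200 for dropout.

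Section 8-5 anticipates a better prognosis than in X-ACT. Its procedure is that "we estimated DFS Kaplan-Meier curves for both groups using the latest data as early as possible before enrolling the target number of subjects". The curves are compared with X-ACT, and the number of subjects is revised if events are clearly too few. On resizing, "the magnitude that appears to be clinically appropriate will be reviewed as an additional effect expected for group B", measured against the Group A 5-year rate. The section gives no numerical trigger and no upper or lower limit. It does not say who sees the curves or how the error rate is protected.

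Section 8-7 names three interim analyses and a final one. Only the first interim falls during enrolment, and there "the effectiveness of the first intermediate analysis is not evaluated". On the error rate, "test multiplicity for the interim and final analyses was adjusted using" a Lan-DeMets spending function of O'Brien-Fleming type, to hold 5% overall. The 8-5 review is not on that list. Section 8-6 separately allows enrolment and follow-up to be extended if subjects or events fall short.

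**The concern.** The question in 8-5 is whether events arrive too slowly. The combined DFS curve and event count answer it without showing which arm the events come from. The procedure as worded shows outcome by arm, and in the same step reopens both the size of the trial and the difference it is meant to detect.

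If the final amount of information can depend on the interim difference, an ordinary log-rank test at the end is not guaranteed to keep its 5% level. The leverage is large. In Table 8-1, at 60% in Group A, moving from a 7-point to a 5-point gain takes the total from 1,142 to 2,272 patients, a factor of 1.99. Even if nobody used the by-arm information, a later change of size or target could not be shown to be independent of it.

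**Working it through.** **Inputs from the protocol.** 5-year DFS 60% and 67%; equal hazards for 0.5 years; 2 years of enrolment and 5 of follow-up; one-sided 5%; 480 events; 1,200 enrolled (8-4). **Assumptions of this check.** Uniform enrolment, a look at 12, 18 or 24 months, and a final event count between 480 and 960. The protocol gives no look date and no limits.

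**1. Design model.**
- Group A hazard: λA = −ln(0.60)/5 = 0.1022 per year.
- Group B hazard after 6 months: λB = (−ln 0.67 − 0.5 × 0.1022)/4.5 = (0.4005 − 0.0511)/4.5 = 0.0776.
- Post-6-month hazard ratio: 0.0776/0.1022 = 0.76.
- Check against the plan: 1,142 subjects followed to year 7 give 478 expected events; the plan states 480.

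**2. What by-arm curves would show during enrolment** (1,200 subjects over 2 years, design assumptions true).

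| Look | Enrolled | DFS events | of which in months 0–6 |
|---|---|---|---|
| 12 months | 600 | 29 | 22 (78%) |
| 18 months | 900 | 62 | 37 (60%) |
| 24 months | 1,200 | 107 | 52 (49%) |

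Between half and three quarters of the events come from the period in which 8-4 assumes no difference. Splitting them by arm adds almost nothing to planning. The total says whether the event rate is on course.

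**3. Upper bound on the error.** Let Z1 be the by-arm log-rank statistic at D1 events. Under no difference, a final unadjusted test at D events rejects with conditional probability

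P(reject | Z1, D) = Φ[(Z1√D1 − 1.645√D)/√(D − D1)].

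For each Z1, take the D between 480 and 960 that maximises this, then average over the standard normal distribution of Z1. With D fixed at 480 the formula returns 5.0%, as it should.

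| Look at | Worst-case one-sided error, final count 480–960 |
|---|---|
| 29 events | 5.3% |
| 62 events | 5.5% |
| 107 events | 5.6% |

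The calculation uses a single final test at 1.645 and leaves out the later interim analyses.

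**4. Would adding the look to the spending plan cure it?** No. The O'Brien-Fleming-type spend at information fraction t is 2[1 − Φ(1.96/√t)]. At 62/480 = 0.13 this is below one in ten million; at 240/480 it is 0.0056. Charging alpha for the look costs nothing and repairs nothing, because the inflation comes from choosing the final size after seeing the arms.

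**5. Can the target effect simply be frozen?** Not in both forms at once. If Group A is at 70% rather than 60%, then λA = −ln(0.70)/5 = 0.0713. A 7-point gain then needs a post-6-month hazard ratio of 0.70, while a hazard ratio of 0.76 gives exp(−0.0713 × 0.5 − 0.76 × 0.0713 × 4.5) = 75.6%, a gain of 5.6 points.

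**The case against.** The case for leaving 8-5 alone has real substance.

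- **A reader might infer an unplanned efficacy look.** The text does not support that. Section 8-5 contains no test of A against B, no boundary and no efficacy stop; its comparator is X-ACT and its trigger is a lack of events.
- **A reader might infer a contradiction with 8-7.** That does not follow either. The statement that efficacy is not evaluated concerns the first interim analysis, which 8-5 does not mention. Both can hold.
- **A reader might infer that the investigators learn by-arm results.** Section 8-5 does not say who sees the curves. The data center runs the interim analyses, and access rules may sit in a statistical analysis plan not seen here.
- **The English is loose, and curves for both groups may mean the groups combined.** This is possible. The plural and the review of the Group B effect against Group A point the other way, and a single sentence would settle it.
- **The effect review is tied to clinical relevance and is partly unavoidable.** This stands. Step 5 shows that the target must be restated if prognosis is better. What is missing is a statement that by-arm data play no part.
- **The error figures need an adversary.** This also stands. Someone would have to choose, for each interim result, the event count most likely to reject. If subjects are added only to reach a fixed 480 events, the event count is not chosen from the difference and this mechanism does not operate.

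**Conclusion.** The point holds as a moderate one. Section 8-5, as worded, provides for a sample-size revision with outcome visible by arm and the Group B effect open to review. It falls outside the analyses covered by the spending rule and has no stated error protection, for a purpose that the pooled event rate serves equally well.

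The size is small: at most about 5.3–5.6% against the stated 5%, for increases only, on the assumed look at 29–107 events and final count of 480–960. Larger figures can be produced: about 5.9% if the count may fall to 300 (look at 62 events), and about 11% with no limits. Neither fits a revision triggered by too few events, so neither should be set against this plan. The stronger reason to change the text is that any later change of size or target would be open to challenge, and avoiding that costs almost nothing.

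**What to change.** Rewrite 8-5 along these lines:

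1. The review uses the DFS curve and event count with both arms combined, prepared without treatment codes, and compared with X-ACT.
2. The target effect is not revised from by-arm data. Choose one rule and state it: either hold the post-6-month hazard ratio of 0.76 with the 480-event target and restate the absolute gain at the pooled rate, or change the effect only on clinical or external grounds.
3. An event shortfall is met by extending enrolment or follow-up until the event target is reached, as 8-6 already permits.

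The cost is a wording change. The loss of planning information is negligible, since the by-arm split of 29–107 early events says little about the difference.

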## **8-6. Study Period**

Enrollment period: 2 years (Sept. 2008–Aug. 2010)

Follow-up period: 5 years after last enrollment

Cumulative study period: 7 years (Sept. 2008–Aug. 2015)

The registration and follow-up periods may be extended if the number of enrolled subjects is less than the target number or if the number of events is less than the required number.

## **8-7. Interim Analyses and Early Study Termination**

Three interim analyses were conducted for the purpose of evaluating whether enrollment can be continued and whether the primary endpoint of the study has been achieved. The first interim analysis will be performed after half of the number of subjects are enrolled. This analysis will comprehensively evaluate whether enrollment should be continued. However, the effectiveness of the first intermediate analysis is not evaluated. As a general rule, registration will not be suspended during interim analysis.

In the second interim analysis, the main purpose is to evaluate study effectiveness, and this analysis is performed after the 1,200 subjects are enrolled. The second interim analysis will also involve an exploratory analysis that will serve as a reference for the secondary comparative study of the 2-year DFS rate. In this exploratory evaluation, the selection design 31) described by R. Simon is applied, and the selection results are disclosed only to the members of the Data and Safety Monitoring Committee and the researchers recognized by the Executive Committee. However, this disclosure will not affect the verifiability of the primary endpoint of this study, and these results will also be published in the interim analysis.

In the third interim analysis, the main purpose is to evaluate the effectiveness of the study, and this analysis will be conducted after half the number of necessary events (240 events) are observed during the follow-up period. If it is determined that the primary endpoint of the study has been achieved during interim analysis, the study will be terminated and the results of the study will promptly be made public at academic symposia and in academic journals.

Interim analyses are carried out by the data center. To maintain the overall Type I error rate at 5%, test multiplicity for the interim and final analyses was adjusted using Lan & DeMets’ α consumption function 32). The difference in DFS between the groups was examined for statistical significance, but here the O’Brien & Fleming type was used as the α consumption function. During intermediate analysis, when the DFS for group B exceeded that of group A and the one-sided *p*-value of the stratified log-rank test fell below the significance level prescribed by the above method, the result was determined to be statistically significant and the test was terminated as a general rule. If the survival curve for group B is lower than that of group A, judgments are not made based on test results, and the issue of whether to comprehensively terminate the study is made with reference to estimated Bayes flow probability or conditional detection ability.

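### The exploratory 2-year DFS selection is set for the end of a 2-year enrolment, when no patient has more than 2 years of follow-up; it belongs at the 240-event interim

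*Protocol*

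**What the plan says.** Section 8-7 plans three interim analyses. The first comes when half the subjects are enrolled and does not assess efficacy. For the second, "the main purpose is to evaluate study effectiveness", and its timing is given as "this analysis is performed after the 1,200 subjects are enrolled". No follow-up, event-count or data cut-off condition is attached. The same look carries "an exploratory analysis that will serve as a reference for the secondary comparative study of the 2-year DFS rate", using a Simon-type selection design. The selection result goes only to the Data and Safety Monitoring Committee and to researchers recognised by the Executive Committee, and a further clause says the results will also be published. The third interim comes when "half the number of necessary events (240 events) are observed".

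Section 8-6 gives "Enrollment period: 2 years (Sept. 2008–Aug. 2010" and "Follow-up period: 5 years after last enrollment", and allows either period to be extended. Section 8-4 states of the first 6 months after randomisation: "There is no difference in disease-free survival (DFS) during this 6-month period". The last paragraph of 8-7 applies O'Brien-Fleming-type Lan-DeMets spending at an overall 5%. It also says that if Group B's curve lies below Group A's, stopping is considered with the help of predictive probability or conditional power.

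**The concern.** A selection on 2-year DFS needs patients followed for 2 years. If the last of 1,200 subjects enters at month 24, the first is only then reaching 2 years and the average patient has been followed for 12 months. Kaplan-Meier can still return a value near 2 years, but from very few patients at risk, and a rule that picks the arm with the higher estimate will often pick the wrong one.

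The result is exploratory and drops no arm. It is nevertheless shown to some researchers, and apparently published, while the trial continues. An unreliable ranking of the arms at that point can colour views of the trial for years before the primary analysis.

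The same look is presented as an evaluation of effectiveness, yet about half of its expected events come from the period in which 8-4 says the arms do not differ.

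**Working it through.** **Inputs.** From 8-4: 5-year DFS 60% (A) and 67% (B), no difference for 6 months, 480 events, 1,200 subjects (600 per group). From 8-6: 2-year enrolment. From 8-7: one-sided 5% overall with O'Brien-Fleming-type spending. Assumed here: uniform accrual, no dropout, and a constant hazard apart from the change in B at 6 months.

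**Model.**
- Hazard in A: -ln(0.60)/5 = 0.1022 per year.
- Hazard in B: the same to 6 months, then (-ln 0.67 - 0.5 × 0.1022)/4.5 = 0.0776 per year, a late hazard ratio of 0.76.
- 2-year DFS: A exp(-2 × 0.1022) = 81.5%; B exp(-0.5 × 0.1022 - 1.5 × 0.0776) = 84.6%. The true difference is 3.1 points.

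**The plan's own figure.** With 1,142 subjects, 2 years of enrolment and 5 years of follow-up, this model gives 478 events against the stated 480, so the event timeline reproduces. The 1,142 needed for 80% power does not (about 1,016 here), but nothing below uses it.

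**Timeline with 1,200 subjects.** Expected events are 107 at month 24, 202 at month 36 and 288 at month 48; 240 events arrive at about month 41.

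**Selection on 2-year DFS.** Trials with 600 per arm were simulated, the 2-year Kaplan-Meier values compared, and the higher arm picked. Where a curve ends before 2 years, its last value is carried forward.

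| Data cut-off | SD of B - A (points) | Worse arm picked |
|---|---|---|
| Month 24 | about 6 | about 25% |
| Month 27 | about 3.2 | about 17% |
| Month 30 | about 2.7 | about 14% |
| Month 36, 3-year enrolment | about 2.9 | about 14% |
| 240 events (about month 41) | about 2.2 | about 8% |

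At month 24 about 21 patients per arm are at risk at 23 months and none at 24. The estimates are then far from normal, so the 25% comes from the simulation and not from the ratio of difference to SD.

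Waiting to month 48, when every patient has 2 years, gains almost nothing over month 41: the wrong-selection rate is again about 8-9%.

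**Efficacy test at month 24.**
- Information: 107/480 = 22%. About 52 of the 107 events fall in months 0-6.
- Boundary: 2 × [1 - Φ(1.96/√0.224)] = 0.00003 one-sided, z = 3.98. The observed hazard ratio would have to be about exp(-2 × 3.98/√107) = 0.46 or lower.
- Drift from the 55 late events: 0.274 × 55/(2 × √107) = 0.73, where 0.274 = -ln 0.76. Crossing probability: 1 - Φ(3.98 - 0.73) = about 0.06%.

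**Sensitivity (assumed shapes).** A hazard 2-3 times higher throughout years 0-2 gives 149-171 events (31-36% information). Ramped accrual, alone or with such a hazard, gives 74-119 events (15-25%). In all these 2-year enrolment cases nobody has more than 2 years of follow-up at month 24.

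**The case against.** **The selection has a modest role.** It is exploratory, drops no arm and changes no treatment; the 2-year DFS endpoint itself is estimated under 8-3. This stands, and it limits the severity. It is also too strong to call the result pure noise: the better arm is still picked about 75% of the time.

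**The cut-off is not stated.** The trigger says only after enrolment, and a lag may be set in the statistical analysis plan. Enrolment may also be extended. Either would bring wrong selection down to about 14-17%. This stands too, though the other two interims are triggered in the same way, so the natural reading is the end of enrolment.

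**The hazard may not be constant.** Section 2-2-4 reports that recurrence risk on 6-month capecitabine peaked between 1 and 2 years. Assuming a year 1-2 hazard 2-3 times the level of the first 6 months, 28-35% of 118-124 events fall in months 0-6, rather than about half. Wrong selection is then 22% at month 24, 11-15% at month 27 and 8-10% at month 30. The weakness at month 24 remains; it fades faster with a lag.

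**A stronger reading of the efficacy test.** A reader might infer that the efficacy test at this look is damaging and must be dropped. The documents do not support that. It spends about 0.00003 of alpha, inflates no type I error and leaves power essentially intact; a tiny early crossing probability is how this boundary is meant to behave. The look also has another use: 240 events come at about month 41, whereas the last Group B patient finishes 48 weeks of treatment at about month 35-36. The second interim is therefore the only planned comparative DFS look at which the lower-curve review can act while Group B patients are still on treatment.

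**Disclosure is restricted.** The selection result goes to named groups only, and the publication clause reads unclearly. That is fair, but even restricted disclosure gives weight to the ranking.

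**Conclusion.** The point holds for the 2-year DFS selection. As written, and with the planned 2-year enrolment, the selection is made when nobody has passed 2 years. The worse arm is then picked about 25% of the time under the plan's model, against about 8% at an interim that is already scheduled. These figures rest on uniform accrual, near-constant hazards and no cut-off lag; a lag of 3-6 months or a 3-year enrolment softens the 25% to about 14-17%.

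The efficacy test has about 22% information and almost no chance of stopping for benefit, so 8-7 oversells it as an evaluation of effectiveness. That is a matter of description, not of error control. A reader might conclude that the trial's primary inference is compromised; it is not, because the primary endpoint, type I error and power are untouched. Severity: should-fix, not must-fix.

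**What to change.** In 8-7, move the 2-year DFS selection, and any disclosure or publication of it, to the 240-event interim. If 2 years after last enrolment is preferred (about month 48, 288 events), reorder or merge the looks, because that date falls after the present third interim.

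Keep the end-of-enrolment look for conduct and safety. The efficacy test and the lower-curve review may stay, with a sentence saying that the information fraction is expected to be about 22% and that stopping for benefit is very unlikely.

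Cost: rewording of 8-7, and an exploratory result about 1.5 years later (month 41 instead of 24), or 2 years later with the month-48 option. Alpha, power and the final analysis do not change.

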# **7. Study Endpoints**

## **7-1. Primary Endpoint**

**7-1-1. Disease-free survival (DFS)**

1) Definition

The period from the enrollment date to the date of the first event confirmation.

2) Event definition

An event is defined as an instance of any of the following:

(1) Recurrence

(2) First occurrence of non-recurrent cancer lesions after the date of enrollment

(M cancer is not treated as a cancerous lesion)

(3) Death from any cause

Surviving subjects not deemed to exhibit cancerous lesions other than recurrences will be determined to have no cancerous lesions as of the final monitoring date.

3) Definition of relapse and recurrence date

Recurrence findings that fall under any of the following are defined as "recurrence". However, if possible, it is advisable to check recurrence via biopsy.

(1) Imaging diagnosis: Confirmation of recurrence based on imaging findings; the date diagnosis was determined is considered the recurrence date.

(2) Pathological diagnosis: If diagnosis of recurrence is made clinically prior to biopsy, the date of diagnosis is considered the recurrence date. If diagnosis could not be made and biopsy enabled diagnosis of recurrence, the biopsy date is considered the recurrence date.

(3) Clinical judgment: If recurrence cannot be confirmed by imaging diagnosis or pathological diagnosis because of rapid deterioration or transference, and clinical findings are reference only, the date of confirmation shall be the recurrence date. However, in such cases, the clinical findings that resulted in the judgment of recurrence should be recorded in the case report along with the confirmation date.

Recurrence does not include increases in tumor marker values.

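### Protocol 8-7 lets a by-arm 2-year DFS selection result leave the Data and Safety Monitoring Committee, and perhaps be published, before the primary DFS analysis, with no release date, firewall or boundary condition

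*Protocol*

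**What the plan says.** Protocol 8-7 plans three interim analyses. Of the second it says that "this analysis is performed after the 1,200 subjects are enrolled". Besides the formal efficacy look, it contains "an exploratory analysis that will serve as a reference for the secondary comparative study of the 2-year DFS rate", carried out as a Simon-type selection design.

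On who learns the outcome, 8-7 says that "the selection results are disclosed only to the members of the Data and Safety Monitoring Committee and the researchers recognized by the Executive Committee". The next sentence adds that "this disclosure will not affect the verifiability of the primary endpoint of this study, and these results will also be published in the interim analysis".

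For the third interim analysis, 8-7 ties public release (meetings and journals) to a finding that the primary endpoint has been achieved and to termination of the study. The selection result carries no such condition.

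On timing, 8-6 gives a 2-year enrollment period and "Follow-up period: 5 years after last enrollment". No data cut-off or release date is set for the second interim analysis.

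**The concern.** Two things look wrong.

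First, the two sentences on disclosure do not fit together. A result restricted to named groups cannot also be published, unless publication here means something narrower than public release. The protocol does not say which is meant.

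Second, the protocol asserts that disclosure is harmless and gives no reason. A selection design names the arm that is numerically ahead, without requiring significance. If the two durations are equally effective, it names Group B about half the time. So 8-7 controls type I error with an O'Brien-Fleming type spending function and, alongside it, lets out an uncontrolled comparison on the same variable as the primary endpoint.

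Knowledge of the favoured duration could affect whether Group B patients complete 16 courses, whether patients stay in follow-up, and how readily a suspected recurrence is worked up and dated. Such effects could differ by arm, and the stratified log-rank test in 8-2 cannot remove them. Section 8-6 also allows follow-up to be extended if events fall short, and nothing keeps people who know the result out of that decision. The trial decides whether Group B replaces the standard therapy (8-2), and disclosure cannot be undone.

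**Working it through.** **Inputs from the protocol.** 600 patients per group; 5-year DFS of 60% (A) and 67% (B); equal hazards for the first 6 months; 480 required events among 1,142 subjects (8-4). Enrollment 2 years, then 5 years of follow-up (8-6). Planned treatment of 24 weeks (A) and 48 weeks (B) (7-2-4), starting within 14 days of enrollment (4-2). **Assumptions added here:** uniform accrual, and no dropout or early stopping of treatment.

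**Hazards.**
- Group A, and both groups to 6 months: −ln(0.60)/5 = 0.1022 per year.
- Group B after 6 months: (−ln 0.67 − 0.5 × 0.1022)/4.5 = 0.0776 per year.
- Hazard ratio after 6 months: 0.0776/0.1022 = 0.76.

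**Check against the protocol's own figure.** Averaging 1 − S(follow-up) over follow-up times spread evenly from 5 to 7 years gives 274.4 + 227.7 = 502.1 events in 1,200 patients. Scaled to 1,142 patients: 502.1 × 1,142/1,200 = 478, against the stated 480. The event model therefore matches the plan's. (On the number required for 80% power, Gehan weights give 1,155 subjects and 483 events, close to the stated 1,142 and 480; an unweighted log-rank gives 1,017 and 425. The present point does not depend on this.)

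**Events outstanding at the second interim analysis.** For a cut c years after enrollment closes, follow-up is uniform on (c, c + 2). Expected events = 600 × mean(1 − S_A) + 600 × mean(1 − S_B).

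| Cut after enrollment closes | Events A + B | Total | Share of 480 outstanding | Patients with 2 full years |
|---|---|---|---|---|
| 0 months | 57.3 + 50.1 | about 108 | 78% | none |
| 6 months | 84.4 + 71.9 | about 156 | 67% | 25% |
| 12 months | 110.0 + 92.0 | about 202 | 58% | 50% |
| 24 months | 157.6 + 130.0 | about 288 | 40% | all |

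At the earliest cut, about 1,200 − 108 = 1,092 patients are still event-free.

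**Group B patients still in the planned treatment window.** Two years is 104.4 weeks.
- Cut and release at 0 months: 48/104.4 × 600 = 276. With the full 14-day start lag: 50/104.4 × 600 = 287 to 288.
- At 6 months (26.1 weeks): (48 − 26.1)/104.4 × 600 = 126, or about 138 with the lag.
- At 12 months: none. The window closes 48 to 50 weeks, or about 11 to 11.5 months, after the last enrollment.

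These are upper figures, because patients who stop early are not removed.

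**How exposed the endpoint is.** No blinding or placebo is described, and 8 courses cannot be mistaken for 16. No central review of recurrence is described in 6-3 or 7-1-1. Recurrence may be accepted on this ground: "Clinical judgment: If recurrence cannot be confirmed by imaging diagnosis or pathological diagnosis because of rapid deterioration or transference". Section 5-5-1 lets patients ask to stop treatment and physicians stop it when they judge this necessary; 5-5-2 recognises withdrawal of consent to follow-up.

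**The case against.** The strongest reply is that the passage can be read narrowly. Disclosure is "disclosed only to the members of the Data and Safety Monitoring Committee and the researchers recognized by the Executive Committee", and nothing says that treating physicians at the sites are told. Publication in the interim analysis may mean inclusion in an interim report: where 8-7 means public release, it names meetings and journals, and section 15 routes publications through foundation committees. The selection is expressly exploratory, and formal stopping is governed separately by the spending function.

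Much of this stands, and it limits what can be claimed. A reader might infer the following, none of which the protocol supports as fact:

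- **That the result goes to site investigators and the public.** The text names a restricted group, and the publication sentence is ambiguous. Equally, the text does not exclude treating physicians from the recognized researchers, nor public release.
- **That release falls while patients are on treatment.** No date is set. At the close of enrollment nobody has 2 full years of follow-up, so a 2-year comparison might well wait; after about 11.5 months no patient is in the planned treatment window.
- **That 78% of events are always outstanding.** That is the earliest-cut figure; the range is 40% to 78%.
- **That recurrence rests freely on clinical opinion.** Clinical judgment applies only where imaging or pathology cannot confirm recurrence for the stated reasons, and the findings must be recorded. Rises in tumor markers do not count, biopsy is advised where possible, both arms share one surveillance schedule, and DFS includes death from any cause.
- **That the primary result will be biased by a known amount.** The figures count exposed patients and events; they do not measure an effect on the hazard ratio or on type I error.

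The reply does not meet the core point. Even on the narrow reading, a by-arm result on the primary endpoint's own variable leaves the monitoring committee before the primary analysis, without a condition, a date or a firewall.

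**Conclusion.** The concern holds in a limited form. Section 8-7 lets a by-arm 2-year DFS selection result go beyond the Data and Safety Monitoring Committee before the primary analysis. It leaves restricted disclosure and publication unreconciled, and offers only an unsupported assertion that the primary endpoint is safe. At every data cut examined, from 0 to 24 months after enrollment closes, a large share of the primary-endpoint evidence is still to come. DFS follow-up would be continuing at all these dates; treatment would be continuing only if cut and release came within about 11.5 months of the last enrollment.

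The event range rests on the protocol's 60%/67% model and on uniform accrual; the treatment-window counts rest on uniform accrual and full treatment duration. That the trial is open-label is inferred from the design, not stated. The documents show an avoidable exposure; they do not show that bias will occur. This is a cheap improvement worth making before the second interim analysis.

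**What to change.** In Protocol 8-7:

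1. Reconcile the two disclosure sentences. If publication was meant as inclusion in an interim report, say so and limit that report to the recipients in item 2.
2. State that all by-arm interim DFS results, including the selection result, stay with the Data and Safety Monitoring Committee and the statistician who prepares them.
3. State that the study representative and the Executive Committee receive only a recommendation to continue, modify or stop.
4. State that by-arm results are published only after the primary analysis, or after a boundary is crossed and the trial is formally stopped.
5. Delete the assertion that disclosure has no effect on the primary endpoint.

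The cost is a few sentences in one section, with no change to sample size, data collection or the primary test. The one real loss is early release of the exploratory 2-year result.
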